## The intervention

The randomised controlled trial will involve two parallel arms, an intervention arm and a control arm. The intervention arm will receive the 6 month text message intervention (DTEXT). Both arms will receive usual care from their treating doctor and associated health professionals.

The text message intervention was developed by an expert panel of clinicians, academics and health promotion staff using evidence-based guidelines and recommendations [7], and the use of appropriate language for Australian adults with type 2 diabetes [47, 48]. The content of the messages has a readability level of grade 5–6 (10–11 years of age) [49]. Each text message was limited to 160 characters in length, and no message was repeated during the intervention. The messages were tested with 20 people with type 2 diabetes in a 5 week pilot program to determine message acceptability and ensure message content, tone and structure was appropriate. Adjustments to the messages were made based on pilot participant feedback.

The DTEXT text messages were designed using Michie et al’s COM-B system from the Behaviour Change Wheel [50]. This system increases the individual’s capability, opportunity and motivation to enhance their self-management of health and lifestyle related behaviours, with the aim to improving diabetes control. Individual behaviour change is a critical component to achieve self-management of conditions [20]. The behaviour change techniques used in the text messages were based on the Behaviour Change Technique Taxonomy [51] and include: providing information about the health consequences, prompts and cues, problem solving, self-monitoring of behaviour and outcome, goal setting of behaviour and outcome, instruction on how to perform a behaviour, graded tasks, social support, social comparison, self-talk, credible source and reducing negative emotions. Behaviour change techniques are recommended for disease management programs using mobile technology [52].

The text message intervention will consist of daily text messages for months 1–3; and four messages per week for months 4–6. The messages will be designed to be sent at random times between 8 am and 5 pm, with message themes coinciding with relevant times of the day e.g. breakfast messages sent in the early morning, healthy dinner options sent in the afternoon. They include modules on nutrition, physical activity and sedentary behaviour, diabetes care and compliance with the diabetes Annual Cycle of Care, weight management, medication adherence and smoking cessation. The messages will be semi-personalised with occasional use of the participant’s name receiving the messages, occasional use of the researcher’s name ([name]) sending the messages, and tailored so that only smokers receive smoking cessation messages and only those taking medication will receive medication adherence messages (see Table 1).

**Table 1 Tab1:** Summary of the 6 month DTEXT intervention

Module	Description	Number of Messages n (%)	Example message
Nutrition	Up to 3 messages a week on dietary advice and recommendations; eating out; portion size; example meal, snack and drink options.	47 (35)	For good health, aim to eat 5 serves of vegetables each day. 1 serve = half a cup cooked vegetables or 1 cup salad vegetables. Try eating some with each meal.
Physical activity	Up to 3 messages a week on physical activity advice and recommendations; reducing sedentary time; goal setting; free or home based activities; community programs and support.	47 (35)	Hi (name), Did you know by walking up 2 flights of stairs per day you can lose 3 kg a year? Are there any stairs nearby you could try? [name]
Diabetes care	Up to 2 messages per week on: self-management; completing the Annual Cycle of Care; and accessing health professionals for care and support.	26 (20)	HbA1c tests are the best measure of your diabetes control. Aim to keep HbA1c under 7% or 53 mmol and have it tested each year. Ask your doctor about your HbA1c.
Weight management	Up to 1 message per week with motivation and guidance to achieve and maintain a healthy weight range.	13 (10)	Sugary drinks (soft drink, sports drink, cordial) can lead to weight gain – a 600 ml soft drink bottle has 16 teaspoons of sugar!
Medication adherence	Up to 1 message per fortnight with support for medication adherence; filling scripts; seeking advice for adverse effects; and undertaking an annual medication review.	9 (additional messages for medication users)	Have you taken your diabetes medication today? Try using a calendar reminder or ask a pharmacist about a weekly pill box to make taking your medication easier.
Smoking cessation	Up to 1 message per fortnight with advice, motivation and support for quitting smoking; and accessing community support programs.	9 (additional messages for smokers)	For help quitting smoking call the Quitline on [name]. Quitline staff are trained to help you manage your journey to better health.

A technology platform to deliver text messages will be developed using the software company Message Media. The platform will allow for automation of the text message intervention. The intervention will be designed as a uni-directional program, however participants will be able to reply to text messages with responses addressed by the study team, if required. Participants can withdraw from the study at any time using an automated opt-out STOP function.

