### Sample size

The required sample size of 340 (170 per arm) will provide 80% power of detecting a between-group change in HbA1c of 0.7%, allowing for 20% loss to follow up and an alpha = 0.05.

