### Outcomes measures

#### Primary outcome

The primary outcome measure will be change in HbA1c, determined by blood test at baseline, 3 and 6 months. Blood tests will occur at the participant’s local pathology collection centre, and a copy of the results will be sent to their doctor for consultation and follow up with their patient if required. Participants will receive a $25 store voucher upon receipt of pathology results.

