### Statistical analysis

Statistical analysis will be conducted using the software programs Statistical Package for the Social Sciences (SPSS-25) and Statistical Analysis System (SAS) v9.4, with an intention to treat principle.

Generalised estimating equation (GEE) models will be used to assess impact, modelling repeated outcome measures over time. Change in HbA1c will be analysed using GEE models to test the effect of the intervention on change in HbA1c between the two groups.

GEE will also be used to assess the effect of group allocation on changes over time in BMI, TC, LDL-C, HDL-C, TG, physical activity, dietary behaviour, smoking status, quality of life, self-efficacy measures and use of health services after adjusting for baseline scores. Two planned subgroup analyses will be undertaken to assess differential impact of the intervention on the basis of age and sex.

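### STOP on the message platform is worded as leaving the study, a route only the intervention arm has, so follow-up HbA1c may be lost unevenly between the arms

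*Protocol article*

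**What the plan says.** The sentence at issue closes the text below Table 1 in The intervention: "Participants can withdraw from the study at any time using an automated opt-out STOP function". It follows directly on the description of the message-delivery software, of which the article says: "The platform will allow for automation of the text message intervention". What the participant is said to leave is the study, not the messages.

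Earlier in the same section the messages are assigned to one arm: "The intervention arm will receive the 6 month text message intervention (DTEXT". The comparison condition is given as "Both arms will receive usual care from their treating doctor and associated health professionals". No messages are described for controls.

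Primary outcome defines the endpoint as "change in HbA1c, determined by blood test at baseline, 3 and 6 months", with blood taken at the participant's local pathology centre. Statistical analysis states that the work will be done "with an intention to treat principle" and that "Generalised estimating equation (GEE) models will be used to assess impact, modelling repeated outcome measures over time". Sample size allows one figure of 20% for loss to follow-up, not split by arm.

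**The concern.** Stopping a treatment and leaving a trial are different events, and an intention-to-treat comparison needs outcomes after the first. Here one automated action is worded as doing both, and it belongs to a platform that only one arm is described as using. Someone tired of the texts who sends STOP would, on the literal reading, leave follow-up as well. A control has no texts to stop and no equivalent one-step exit.

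The loss would be avoidable, because an HbA1c drawn at a pathology centre does not depend on receiving messages. It would also be hard to repair. Analysis by allocated arm does not restore values that were never collected. A GEE without weighting or imputation is generally exposed when missingness depends on the outcome beyond what the model's covariates explain.

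Other results draw on the same follow-up. Process evaluation takes satisfaction and engagement from the 3- and 6-month telephone questionnaire, so people who rejected the messages could be missing from the acceptability results. The end-of-trial SF12v2, used for QALYs, could be lost in the same way.

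**Working it through.** **The plan's own figure.** Sample size gives 340 in total, 170 per arm, for 80% power, a 0.7-point difference, alpha 0.05 and 20% loss. No SD is printed, so the figure cannot be reproduced directly. Evaluable per arm: 170 × 0.80 = 136. Solving back for a two-sided test: SD = 0.7 / (1.960 + 0.842) × √(136/2) = 2.06. This SD is used below only as a working value, with 1.5 as an assumed alternative.

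**Bias.** Let p be the share of the intervention arm lost through STOP. Let D be the amount by which their mean HbA1c change is worse than that of those who stay.

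- Full-arm mean benefit = (1 − p) × B + p × (B − D) = B − pD, where B is the mean benefit of those who stay.
- Observed mean benefit, stayers only = B.
- Bias = p × D.

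The article gives neither p nor D; both are assumptions.

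| p (of 170) | D | Bias, HbA1c points | Share of 0.7 |
|---|---|---|---|
| 5% (8.5) | 0.5 | 0.025 | 4% |
| 10% (17) | 0.5 | 0.05 | 7% |
| 20% (34) | 0.5 | 0.10 | 14% |
| 10% (17) | 0.7 | 0.07 | 10% |
| 20% (34) | 0.7 | 0.14 | 20% |

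The D = 0.7 rows represent stoppers who gain nothing while stayers gain the full planned effect. All rows assume that no follow-up HbA1c is obtained from those who stop and that controls have no matching selective loss.

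**Type I error.** Suppose the messages have no effect, but those who stop would have done 0.5 points worse in any case. Take 10% other loss in each arm. Then SE = SD × √(1/n_I + 1/n_C), with n_C = 153 and n_I = 153 × (1 − p). The two-sided error is Φ(−1.96 + pD/SE) + Φ(−1.96 − pD/SE).

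| p | SD 2.06 | SD 1.5 |
|---|---|---|
| 5% | 5.1% | 5.2% |
| 10% | 5.5% | 5.9% |
| 20% | 6.9% | 8.5% |

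For example, at p = 20% and SD 2.06: SE = 2.06 × √(1/122.4 + 1/153) = 0.25, pD/SE = 0.10/0.25 = 0.40, and the error is 6.9%.

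**Power at SD 2.06.**

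| Loss, intervention / control | Evaluable | Power |
|---|---|---|
| 20% / 20% | 136 / 136 | 80.0% |
| 30% / 10% | 119 / 153 | 79.4% |
| 30% / 20% | 119 / 136 | 77.2% |
| 40% / 20% | 102 / 136 | 73.7% |

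Imbalance at the same overall loss costs almost nothing. Extra loss in the intervention arm costs some power. The main issue is bias, which a larger sample would not remove.

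**The case against.** The sentence may be loose wording. An automated opt-out is an ordinary messaging feature, the paragraph is about the platform, and the article nowhere says that blood tests, questionnaires or record linkage end after STOP. The article also condenses a fuller protocol that is not shown, and follow-up after withdrawal is commonly set out there. This stands as a reason for caution about what will happen in practice. It does not remove the point, because the article is not silent: it states a rule, and the rule names the study.

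A reader might go further and infer that the design creates one-sided loss of the endpoint. The text does not support that. Controls can also withdraw or be lost, participants in both arms are unblinded, no STOP rate is given, and the store voucher for pathology results is not restricted to one arm. What is shown is a risk of differential loss.

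A reader might also infer that the intention-to-treat statement is contradicted. It is not. As a rule for analysing people by allocated arm it is compatible with missing outcomes; what is threatened is the completeness of the data it relies on.

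The size and direction are open to challenge too. A p of 20% equals the whole loss allowance for the arm. Someone who stops after month 3 may already have a 3-month HbA1c in the model. If D arises only because stoppers forgo a real benefit, D is zero when the messages do nothing, and no false positive follows. The type I error figures need stoppers who would have done worse regardless. People could also stop because they feel well controlled, which would push the bias the other way. All of this stands, and it limits the numbers to illustration.

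**Conclusion.** The point holds as a defect of wording with a real consequence if followed. The STOP sentence merges message opt-out with study withdrawal, through a route described for one arm only, and so puts the follow-up HbA1c at risk of treatment-related missingness.

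The size cannot be fixed from the documents. Under the stated assumptions it runs from 0.025 to 0.14 HbA1c points, about 4% to 20% of the 0.7-point target. It is small at low STOP rates. The direction is likely, but not certain, to favour the intervention. It is worth correcting because HbA1c not drawn at 3 or 6 months cannot be recovered later; sensitivity analyses can only bound the damage.

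**What to change.** Reword the sentence below Table 1 so that STOP ends the text messages only. State that the 3- and 6-month HbA1c and questionnaire are still sought from anyone who stops the messages, unless that person separately withdraws consent to follow-up. Record message opt-out and study withdrawal as two events, and report each by arm. If the participant information and the automated STOP reply (neither is shown) carry the same wording, align them.

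If the full protocol already works this way, one clarifying line in the article is enough. Otherwise the cost is the wording change and a small number of extra follow-up contacts with people who stopped the messages. The documents contain no budget, so the cost of those contacts cannot be stated. The right to leave the study at any time is unaffected.

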### Outcomes measures

#### Primary outcome

The primary outcome measure will be change in HbA1c, determined by blood test at baseline, 3 and 6 months. Blood tests will occur at the participant’s local pathology collection centre, and a copy of the results will be sent to their doctor for consultation and follow up with their patient if required. Participants will receive a $25 store voucher upon receipt of pathology results.

#### Secondary outcomes

Secondary outcome measures will be collected at baseline, 3 and 6 months through objective measures taken by pathology collectors and a self-report telephone questionnaire administered by the research team. The questionnaire was piloted with 10 people and determined to be acceptable by pilot participants and easy to deliver with an appropriate timeframe (10–15 min) by the research team.

#### Secondary outcome measures include

##### Blood lipid profile

This includes total cholesterol (TC), low density lipoprotein (LDL-C), high density lipoprotein (HDL-C) and triglycerides (TG). Lipid results will be assessed according to the recommended guideline levels for people with type 2 diabetes [7].

##### Body mass index (BMI)

Weight and height will be assessed for calculation of BMI (kg/m^2^). Readings will be recorded by standardised pathology collectors at the time of each blood test and through self-reported data collected during the questionnaires. BMI status will be assessed according to the World Health Organisation classifications [53].

##### Physical activity

This will be measured using the validated two-question (2Q) assessment tool. This captures duration, frequency and intensity of activity to determine if people are meeting the current guidelines for physical activity [54].

##### Nutrition

This will be measured using selected questions from the New South Wales Population Health Survey [55] and a question developed specifically for this study. The survey provides detailed information on the health of adults in NSW for planning and evaluation purposes.

##### Smoking status

This will be measured using a question from the World Health Organisation (WHO) Steps Instrument and a question developed specifically for this study. The Steps instrument is used to collect and measure non-communicable disease risk factor data [56].

##### Quality of life

This will be assessed using the Short Form 12-item Health Survey (SF12v2). This multi-purpose survey measures quality of life in terms of functional health and wellbeing and has two subscales addressing psychometric measures of physical and mental health [57]. Preference-based health utilities will be determined from a subset of the SF12 questions, using the UK valuation algorithm [58]. These utility scores will be used to calculate Quality-adjusted Life Years (QALYs) for the economic evaluation.

##### Self-efficacy (physical activity, nutrition and diabetes self-care)

This will be measured by questions developed specifically for this study to determine confidence levels with activities.

##### Medication adherence

This will be measured using a question developed specifically for this study to determine compliance with medication schedules.

### Statistical analysis

Statistical analysis will be conducted using the software programs Statistical Package for the Social Sciences (SPSS-25) and Statistical Analysis System (SAS) v9.4, with an intention to treat principle.

Generalised estimating equation (GEE) models will be used to assess impact, modelling repeated outcome measures over time. Change in HbA1c will be analysed using GEE models to test the effect of the intervention on change in HbA1c between the two groups.

GEE will also be used to assess the effect of group allocation on changes over time in BMI, TC, LDL-C, HDL-C, TG, physical activity, dietary behaviour, smoking status, quality of life, self-efficacy measures and use of health services after adjusting for baseline scores. Two planned subgroup analyses will be undertaken to assess differential impact of the intervention on the basis of age and sex.

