**Methods/Design:**

This randomised controlled trial aims to investigate if a 6 month text message intervention (DTEXT) can lead to improvements in glycated haemoglobin (HbA1c) and diabetes self-management among Australian residents in New South Wales (NSW) with type 2 diabetes. Community dwelling adults (*n* = 340) will be recruited with the primary outcome being change in HbA1c at 6 months. Secondary outcomes include behaviour change for diabetes self-management, self-efficacy, quality of life and intervention acceptability. An economic evaluation will be conducted using a funder plus patient perspective.

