### Participants

Participants will be community dwelling adults with a diagnosis of type 2 diabetes and an HbA1c of 7% (53 mmol/mol) or above, who reside in New South Wales, Australia. Participants must be 18 years or older, own and be able to use a mobile phone, be able to read and speak English, and be able to provide informed consent. Exclusion criterion is pregnancy, to exclude gestational diabetes.

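### Baseline adjustment is stated for the listed secondary outcomes but not for the primary HbA1c analysis, which as written gives up precision that is free to recover

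*Protocol article*

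**What the plan says.** All of this is in the protocol article.

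- **Primary outcome:** "The primary outcome measure will be change in HbA1c, determined by blood test at baseline, 3 and 6 months". The abstract fixes the time point: "the primary outcome being change in HbA1c at 6 months".
- **Statistical analysis, general statement:** "Generalised estimating equation (GEE) models will be used to assess impact, modelling repeated outcome measures over time".
- **Statistical analysis, primary outcome:** "Change in HbA1c will be analysed using GEE models to test the effect of the intervention on change in HbA1c between the two groups". No covariate is named, and the text does not say whether baseline HbA1c is a row of the outcome, a covariate or neither.
- **Statistical analysis, secondary outcomes:** "GEE will also be used to assess the effect of group allocation on changes over time in BMI, TC, LDL-C, HDL-C, TG", followed by further outcomes and ending with "use of health services after adjusting for baseline scores". HbA1c is not listed.
- **Participants:** entry requires "an HbA1c of 7% (53 mmol/mol) or above".
- **Randomisation and blinding:** baseline measures are completed before randomisation. Allocation is in blocks of four, and no stratification by HbA1c is mentioned.

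**The concern.** The article considers baseline adjustment worth stating, yet states it only for secondary outcomes. The sentence for the outcome that decides the trial reads as a plain comparison of change.

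Two things are at stake if it is carried out that way. The confidence interval for the primary effect is wider than the data require. The estimate also stays correlated with any chance difference in HbA1c at baseline, because subtracting the full baseline value over-corrects whenever follow-up regresses towards the mean. Entry on a minimum HbA1c makes such regression likely. Nothing in the described allocation balances baseline HbA1c.

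There is a smaller point about pre-specification. Adjusted and unadjusted models can give different p-values, and the present wording leaves room for either.

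**Working it through.** **1. The plan's own figure.** The Sample size section gives 340 in total (170 per arm), 80% power, a difference of 0.7% HbA1c, 20% loss and alpha 0.05. It gives no standard deviation (SD) and no correlation, so 340 cannot be reproduced directly. Solving backwards, with a two-sided test assumed:

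- Completers per arm: 170 x 0.8 = 136.
- SD = 0.7 / [(1.960 + 0.842) x sqrt(2/136)] = 2.06% HbA1c.

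Putting SD 2.06 back in returns 136 per arm, and 136/0.8 = 170. The figure is coherent with an SD of about 2.06. The article does not say whether that would be the SD of change or of a single measurement.

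**2. Precision.** Let sigma be the common SD at baseline and 6 months and rho their correlation. Per participant:

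- Variance of a change score: 2 sigma^2 (1 - rho).
- Variance after adjusting for baseline: sigma^2 (1 - rho^2).
- Ratio: (1 - rho)(1 + rho) / [2(1 - rho)] = (1 + rho)/2.

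**3. Chance imbalance.** Given a baseline difference D (intervention minus control), the expected change-score estimate is the true effect minus (1 - rho) x D. The adjusted estimate has no such term.

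In the table, rho is assumed. The power column also assumes that 2.06 is the SD of change, so that the unadjusted power is 80%.

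| rho | variance ratio | standard error ratio | adjusted power, 136 per arm | shift of change score if D = 0.3 |
|---|---|---|---|---|
| 0.4 | 0.70 | 0.837 | 91.8% | -0.18 |
| 0.5 | 0.75 | 0.866 | 89.9% | -0.15 |
| 0.6 | 0.80 | 0.894 | 87.9% | -0.12 |
| 0.7 | 0.85 | 0.922 | 86.0% | -0.09 |
| 0.8 | 0.90 | 0.949 | 84.0% | -0.06 |

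At rho = 0.6 the change score needs 1/0.80 = 1.25 times as many participants for the same precision. If 2.06 is instead the SD of a single measurement, change-score power runs from 72.5% (rho 0.4) to 99.3% (rho 0.8), and adjusted power from 86.4% to 99.7%.

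**4. How likely is D = 0.3?** The standard error of the baseline difference with 170 per arm is SD x sqrt(2/170). For assumed baseline SDs of 1.2, 1.5 and 2.06 it is 0.130, 0.163 and 0.223. A difference of 0.3 in either direction is then about 2.3, 1.8 and 1.3 standard errors, with probability about 2%, 7% and 18%.

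**5. Does using GEE change this?** A simulation used 136 per arm, SD 1.5, complete data, an exchangeable working correlation and 400 replicates for each rho. A group-by-time GEE with baseline as an unconstrained outcome row gave the same 6-month estimate as the raw change score. For rho 0.3, 0.5 and 0.7:

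- Empirical standard errors were 0.214, 0.180 and 0.137, against 0.175, 0.152 and 0.127 with baseline as a covariate.
- The slope of the estimate on baseline imbalance was -0.65, -0.51 and -0.31 unadjusted (theory: -0.70, -0.50, -0.30), and 0.06, -0.01 and -0.01 adjusted.

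**The case against.** The strongest reply is that the article never calls the HbA1c model unadjusted. Its sentence names no covariates at all, and the next paragraph says that GEE will *also* be used, which can be read as the same model with baseline adjustment mentioned once. The word *change* settles nothing, because the baseline-adjusted secondary analyses are described as changes over time too. A condensed article may also leave a covariate list to a fuller document. This stands as far as intent goes: that the primary analysis is unadjusted is a reading of the wording, not something the article states. It does not remove the uneven wording, which is in the published text and concerns the primary outcome.

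Four stronger inferences are tempting and not supported:

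- **The primary result would be biased.** Under randomisation the change-score estimator is unbiased and its type I error is valid. Regression to the mean occurs in both arms and does not bias the contrast. The shift in step 3 is conditional on an imbalance actually occurring.
- **The primary outcome gets the least efficient analysis.** For rho above 0.5 a change score is more precise than comparing follow-up values alone, since 2(1 - rho) is then below 1. It is less efficient than the baseline-adjusted analysis, which is the comparison that matters here.
- **The trial is underpowered.** With neither SD nor rho given, no power shortfall can be shown.
- **Baseline must be kept out of the outcome vector.** A longitudinal model with equal baseline means across arms is also sound.

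**Conclusion.** The point holds as a free improvement to the primary analysis, not as an error that invalidates it. Baseline adjustment is written for the listed secondary outcomes and not for HbA1c. If the HbA1c sentence is followed as worded, whether by a change score or by group-by-time with unconstrained baseline, the variance of the 6-month effect is 2/(1+rho) times what baseline adjustment would give: 1.43 at rho 0.4, falling to 1.11 at rho 0.8. A chance baseline difference of 0.3 at rho 0.6 would move the estimate by 0.12, which is 17% of the 0.7 target (0.12/0.7). An imbalance of that size is possible but not common.

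These sizes rest on an assumed rho and on equal variances at baseline and follow-up. In general the gain depends on the slope of follow-up on baseline and disappears when that slope is 1. The asymmetry in the text and the algebra are certain. The sponsor's intention is not.

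**What to change.** State in Statistical analysis that the primary HbA1c GEE takes the 3- and 6-month values as outcomes, with group, visit, group-by-visit and baseline HbA1c as a continuous covariate, and that the between-group contrast at 6 months is the primary test. A longitudinal model with baseline means constrained equal across arms serves the same purpose. Either is acceptable if one is fixed in advance.

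The cost is one sentence. Baseline HbA1c is already collected before randomisation, so no new data or visits are needed. The secondary outcomes already stated as baseline-adjusted need no change, and nothing here requires a change to the sample size. If adjustment was intended throughout, the sentence simply records it.
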